### Monitoring

The monitoring team will include 2 persons, who are not directly working on this trial. They will take responsibility for monitoring–intervention protocol, adverse effects, and enrollment of participants in groups. They will also audit data and carry out any interim analysis. They will report all kinds of changes in study methods and treatment to the Ethical Review Board (IRB) via the principal investigator.

### Safety measures and managing adverse effects

Although it is anticipated that the mentioned protocol won’t result in any serious side effects, the monitoring team will take note of any unexpected occurrences that do happen during or after intervention and will principally inform the relevant specialists about them. The concerned therapist will make a note of it in their record and later let the lead investigator know. Before beginning, the child’s parents will be asked about any food allergies. Any significant negative effects will be noted and published in the trial’s final publication.

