### Study procedure

After the trial registration is obtained, researchers will start the phone call procedure to estimate the willing participants. As the primary screening of cases of “ASD with malnutrition” performed in the population-based survey, the parents will be directly contacted for participating in the trial. From the computer-based random serial, the first 70 ASD will be pooled for enrollment in the study. On the first day, an assessor blinded to group allocation will further screen and take a pre-test assessment. Then the participant will be treated in a multi-disciplinary approach with the consultation of a nutritionist, physiotherapist (PT), Occupational therapist (OT), and speech and language therapist (SLT). Both structured dietary treatment and regular therapy will be provided as three 45 minutes sessions per week for a total of 12 weeks. After 12 weeks, the post-test data will be obtained by the assessor. There will be a follow-up evaluation after 6 months of post-test. There will be a separate assessor for each of the treatment set-ups. The Consolidated Standards of Reporting Trials (CONSORT) manual will be followed when conducting the study. Fig 2 provides a summary of the study’s methodology.

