*Protocol for UD+ RT group*. The group will receive Regular therapy as per the above protocol, but they will not receive any consultations from the nutritionist and will take the usual diet. After completion of the follow-up, they will be advised of the structured diet intervention based on the study result.

*Progression of interventions*. The intervention duration will be 12 weeks. 45 minutes of the session with the ASD Adolescents and their parents will be provided 3 times a week for each therapeutic intervention item. Participants will receive separate sessions for each therapy item (PT, OT, SLT, SD). The progression of interventions will be determined by subsequent professionals.

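### The safety rule covers only undefined unexpected events and publishes only significant ones, is narrower than the Monitoring section, and rests on capture that may differ between arms

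*Protocol article*

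**What the plan says.** The protocol article deals with harms in two places.

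- **Monitoring.** "The monitoring team will include 2 persons, who are not directly working on this trial". Their responsibilities include "adverse effects, and enrollment of participants in groups". The adverse effects are not qualified in any way.
- **Safety measures and managing adverse effects.** After saying that no serious side effects are anticipated, the section states that "the monitoring team will take note of any unexpected occurrences that do happen during or after intervention". It continues: "The concerned therapist will make a note of it in their record and later let the lead investigator know". On reporting: "Any significant negative effects will be noted and published in the trial’s final publication".

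Four other sections bear on who is in a position to notice an event.

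- **Intervention.** "Participants will receive separate sessions for each therapy item (PT, OT, SLT, SD"), three times a week for 12 weeks. The usual-diet arm has no nutritionist consultations.
- **Study procedure.** The structured diet and regular therapy are each described as three sessions a week for 12 weeks. Each set-up has its own assessor. "There will be a follow-up evaluation after 6 months of post-test".
- **Study setting.** One centre serves the control arm and the other serves the experimental arm.
- **Eligibility criteria.** Allergy to the diet is an exclusion. The safety section adds that parents are asked beforehand about food allergies.

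**The concern.** The safety section states two rules, and each acts as a filter. What is noted is limited to occurrences that are *unexpected*; what is published is limited to effects that are *significant*. The article defines neither word, so the person applying it decides.

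The harms most likely to follow from a gluten-free, casein-free and soy-free diet with supplements are not surprising ones. The article itself foresees food reactions, since it screens for allergy. An event that is foreseen and not serious can fail both filters.

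The second worry is unequal observation. The arm that receives the diet may also have more sessions with people who could record a complaint, and those extra sessions are with the professional most likely to hear about diet. Each arm has its own centre, so local habits of recording cannot be separated from treatment.

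What is at stake is the harm side of the conclusion. If the result is favourable, the article plans an awareness programme (Dissemination), a contribution to national guidelines (Discussion) and structured-diet advice for the control arm (Intervention). Events not written down when they occur are hard to recover later.

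**Working it through.** The safety text contains no figure to reproduce. The check sets the two sections side by side and then counts the scheduled contact.

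**1. Scope of recording and reporting**

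| | Monitoring section | Safety section |
|---|---|---|
| Who | two-person monitoring team | the same team, then the therapist concerned |
| What is covered | adverse effects, unqualified | unexpected occurrences |
| What is published | not stated | significant negative effects |

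Take a foreseeable, non-serious event such as food refusal. It is covered under Monitoring. Under the safety section read literally, it need not be noted and is not promised publication. The two scopes differ, and a fuller document could not make the narrower wording cover expected events without changing it.

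**2. Scheduled sessions per participant by arm**

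Formula: session types × 3 per week × 12 weeks.

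- Intervention section, nutritionist counted: structured diet 4 × 3 × 12 = 144; usual diet 3 × 3 × 12 = 108; ratio 144/108 = 1.33.
- Study procedure, read as three diet sessions plus three regular-therapy sessions a week in total, nutritionist counted: 2 × 3 × 12 = 72 against 1 × 3 × 12 = 36; ratio 2.0.
- Nutritionist not counted as a therapist concerned: 108 against 108, or 36 against 36; ratio 1.0.

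**3. Time without scheduled sessions**

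Sessions cover 12 weeks. The follow-up assessment is 6 months (about 26 weeks) after the post-test, so at about week 12 + 26 = 38. The interval without scheduled sessions is 26/38 = 68% of the observation period.

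**4. What unequal contact could do (illustration only)**

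Assume that true harm is equal in the two arms, that an event lasts one week, and that every session has the same independent chance *c* of leading to a note. The chance of capture over *k* sessions is 1 − (1 − *c*)^*k*. In one week *k* is 12 against 9 on the first reading, and 6 against 3 on the second. The values of *c* are assumptions; the article gives none.

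| *c* | 12 v 9 sessions | ratio | 6 v 3 sessions | ratio |
|---|---|---|---|---|
| 0.02 | 21.5% v 16.6% | 1.30 | 11.4% v 5.9% | 1.94 |
| 0.05 | 46.0% v 37.0% | 1.24 | 26.5% v 14.3% | 1.86 |
| 0.10 | 71.8% v 61.3% | 1.17 | 46.9% v 27.1% | 1.73 |
| 0.20 | 93.1% v 86.6% | 1.08 | 73.8% v 48.8% | 1.51 |
| 0.50 | 100.0% v 99.8% | 1.00 | 98.4% v 87.5% | 1.13 |

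With no true difference, the apparent risk ratio runs from 1.00 to 1.30 on the first reading and from 1.13 to 1.94 on the second. It is 1.00 throughout if the nutritionist's sessions do not count. The documents do not allow a choice among these.

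**The case against.** The strongest reply is that the safety sentence is being read too technically. It follows the statement that no serious side effects are anticipated, so *unexpected* may simply mean anything that happens despite that expectation, and the Monitoring section already gives the team adverse effects in general. This is a fair reading of intent. It does not remove the difference in wording, and it does nothing about the publication sentence.

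Second, the monitoring team is named before the therapist, and no arm-specific contact is stated for it. The contact difference then matters only so far as capture depends on providers, and only if the nutritionist is one of the therapists concerned. Study procedure lists the nutritionist alongside the three therapists as a separate profession, while the Intervention section counts the diet sessions as a therapy item. The point is open. It limits the claim to a possible difference.

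Third, event forms, grading and harms tables are commonly left to a full protocol or analysis plan. That is right, and their absence is not the complaint. The complaint concerns rules that the article does state.

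A reader might also infer more than the text supports:

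- *That recording ends at week 12.* It does not. Events after the intervention are expressly to be noted, and there is a later assessment. Only the scheduled sessions stop, and the article attaches no safety task to that later assessment.
- *That the comparison will be biased.* The article states no formal comparison of harms, and the direction and size of any bias depend on an unknown capture rate.
- *That the trial could not speak to its expectation of no serious side effects.* A serious event would be both unexpected and significant, so it would pass both filters.
- *That weight loss would be missed.* BMI is a primary outcome measured in both arms.

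**Conclusion.** The concern holds in a limited form. The safety section's rules are narrower than the Monitoring section's, rest on two undefined words, and taken literally allow foreseeable non-serious diet harms to go unrecorded or unpublished. That conclusion needs no assumption beyond the text.

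A difference in ascertainment between arms is possible but not shown. It rests on three assumptions: that providers are an effective route of capture, that the nutritionist counts among them, and that capture per session is well short of complete. The one-centre-per-arm layout adds a further possible difference that cannot be separated from treatment. The size is unknown.

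The efficacy analysis is unaffected. The wording should still be changed, because the change is cheap and unrecorded events are hard to recover.

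**What to change.** 1. Reconcile Monitoring with Safety measures and managing adverse effects, so that both say that all adverse events, expected or not, are recorded in both arms.
2. Use one short parent-completed checklist, identical in both arms (gut symptoms, food refusal, food reactions, injury in therapy, other). Give it at a fixed interval at regular-therapy sessions, which both arms attend, and not at the nutritionist's sessions.
3. Give the same checklist at the existing 12-week and 6-month follow-up assessments, covering the time since the last one. This attaches a stated means of capture to the period after week 12.
4. Replace the publication sentence with a commitment to publish all adverse events by arm.

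The cost is a protocol amendment and a one-page form at visits that already take place, with no extra visit or staff. The downside is a few minutes of parents' time and a longer list of minor events. Two limits remain: recall over about 26 weeks will be imperfect, and a common form reduces but does not remove the confounding of centre with arm.

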### Data analysis

According to the nature of the data, SPSS version 23 for Windows will be used for analysis. The distribution of data will be performed using normality indicators and normality tests such as the Kolmogorov-Smirnov test, and the Shapiro-Wilk test. Descriptive analysis will be performed by mean and standard deviation for the continuous data, and frequency and percentage categorical data. The baseline compatibility, between-group post-test, and follow-up variations among the groups will be assessed using MANOVA or the Multivariate Kruskal-Wallis (MKW) test, depending on the nature of the data. Repeated measure or Friedman’s ANOVA Three measures will be analyzed within-group using an ANOVA, and additional post-hoc analyses will be performed using paired sample t-tests or Wilcoxon tests. We will perform the intention to treat the analysis process for the drop-out of cases taking more than one month of interventions. In the case of a post hoc Bonferroni adjustment, the level of significance P < .05 will be converted to P < .0125.

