### Sample size

Sample size calculation has been performed through the software ClinCalc [S1 File] estimating the key outcome as the score of the Gilliam Autism Rating Scale (GARS 2) second edition [23, 30]. Sample size has been calculated [27] as the anticipated minimal clinically important differences (MCID) of GARS-2 [23] were estimated as 4.7±1.7 (0–10 Hiva scale converted from 0–126 GARS 2 score) with a baseline of 25% minimal clinical improvement, enrolment ratio 1:1, 80% power, and with the alpha value 0.05, the total sample stands as of 66. For safety we will enroll 70 ASD adolescents with a number of 35 participants in each group.

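### The collected data decide between MANOVA and a multivariate rank test, with no default or stated rule, and neither directly estimates the mean GARS-2 difference the trial was sized on.

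*Protocol article*

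**What the plan says.** The Data analysis section of the protocol article says that distributions will be examined with normality indicators and "normality tests such as the Kolmogorov-Smirnov test, and the Shapiro-Wilk test". The between-group comparison at post-test and follow-up, like the baseline comparison, "will be assessed using MANOVA or the Multivariate Kruskal-Wallis (MKW) test, depending on the nature of the data". The within-group analyses have the same fork: repeated-measures ANOVA or Friedman's test, after which "additional post-hoc analyses will be performed using paired sample t-tests or Wilcoxon tests".

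The Sample size section treats GARS-2 as the outcome that drives the trial, "estimating the key outcome as the score of the Gilliam Autism Rating Scale (GARS 2) second edition". It takes a value of 4.7 with SD 1.7 on a 0-10 conversion of the scale, "with a baseline of 25% minimal clinical improvement", and then "enrolment ratio 1:1, 80% power, and with the alpha value 0.05, the total sample stands as of 66". Enrolment is raised to 70, or 35 per group. The Primary outcome variables section lists GARS-2 together with anthropometric measures (MUAC and BMI).

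**The concern.** The choice between MANOVA and a rank test is made after the outcome data have been inspected. The section does not say which variables are tested, at which times, per arm or pooled, at what threshold, or which normality test prevails if they conflict. Two analysts following the text faithfully could therefore report different tests as the trial's answer to its third objective, the comparison between groups.

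The second problem is a mismatch with the sample size. The trial was sized on a difference between two mean GARS-2 scores. An omnibus multivariate test over several outcomes, whether on the raw scores or on ranks, gives a statistic and a p-value. It gives no GARS-2 difference with an interval to set against the planned effect. Baseline GARS-2 is measured but used only to check comparability.

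**Working it through.** **1. Reproduce the plan's sample size.** Inputs from the Sample size section: mean 4.7, SD 1.7, 25% improvement, 80% power, alpha 0.05, ratio 1:1. The article does not state one- or two-sided; two-sided is assumed here.

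- Difference = 0.25 × 4.7 = 1.175 points. Standardised, 1.175 / 1.7 = 0.69 SD.
- n per group = 2 × (1.960 + 0.842)² × 1.7² / 1.175² = 32.9, so 33 per group and 66 in total. This matches the article. A one-sided test would give 26 per group and does not match.
- Power of the two-sample t test is 79.0% at 33 per group and 81.3% at 35 per group.

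The stated size is therefore that of a two-group comparison of mean GARS-2, a test the Data analysis section does not name for the between-group question.

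**2. How often normal data would be sent to ranks.** The rule is not stated, so several readings are shown. Each assumes Shapiro-Wilk at 0.05 and that any rejection causes the switch. For k independent checks the chance is 1 − 0.95^k.

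| Reading of the rule | k | Formula | Simulated, n = 35 per arm |
|---|---|---|---|
| GARS-2, one time, two arms | 2 | 9.8% | 9-11% |
| Three outcomes, one time, two arms | 6 | 26.5% | 23-29% |
| Three outcomes, three times, arms pooled | 9 | 37.0% | 35-36% |
| Three outcomes, three times, two arms | 18 | 60.3% | 59% |

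**3. Whether the two named normality tests agree.** For one sample of 35, with the Lilliefors form of Kolmogorov-Smirnov assumed, the two tests gave opposite verdicts in about 6% of normal samples. For mildly skewed samples (gamma, shape 8) the figure was about 20%, and for more skewed samples (gamma, shape 4) about 28-29%.

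**4. Whether the choice changes the answer.** All runs use 35 per arm and a shift of 0.69 SD in GARS-2.

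- Univariate stand-in, t test against Mann-Whitney: different verdicts in about 5% (normal), 6% (gamma 8) and 7.5% (gamma 4) of trials.
- Closer to the named tests, with three uncorrelated outcomes and Hotelling's T² (the two-group MANOVA) against multivariate Kruskal-Wallis: different verdicts in 6.5% of trials with normal data. With strongly skewed data (lognormal, sigma 0.6) it was 22%, and the gate then switched in essentially every trial.

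**5. Type I error.** With the gate applied mechanically it was 5.1% (normal) and 4.8% (lognormal) in the three-outcome runs, and between 4.7% and 6.0% in the univariate runs. Reporting whichever test is significant would give 5.7-6.4% in the three-outcome runs.

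**6. What the omnibus test does to the planned power.** If only GARS-2 shifts by 0.69 SD and the three outcomes are uncorrelated, the noncentrality is 35/2 × 0.69118² = 8.36 on 3 and 66 degrees of freedom. Power is then 65%, against 81% for the GARS-2 comparison the trial was sized on. Correlated outcomes, or effects on BMI and MUAC as well, would change this figure.

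**The case against.** The strongest reply is that little harm follows. The type I error of the two-stage rule is close to nominal, and at the planned effect the two tests usually agree. This stands, and no claim of error inflation is made here.

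A reader might infer that the switch to ranks is what loses the GARS-2 estimate. The article does not support that. MANOVA gives no GARS-2 difference with an interval either, and group means and SDs are planned on either branch, so an unadjusted difference could be computed afterwards. What remains is that neither branch makes that difference the planned result.

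A reader might also infer that going to ranks forfeits baseline adjustment. It does not: no baseline covariate is planned in either branch, and rank analysis of covariance exists.

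Nor can 59% be read as the expected switching rate. It assumes that any one of 18 checks decides. The article does not say so, and its mention of normality indicators leaves room for judgement.

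A rank fallback also has some rationale. Eligibility selects on BMI and excludes severe behavioural problems on GARS-2, so truncated distributions are plausible. That supports a rank-based sensitivity analysis, not a choice of main test left open until the data are seen.

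Finally, a separate analysis plan might settle the threshold and the estimator. But the article does not merely omit the method: it states a data-dependent choice for the main comparison.

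**Conclusion.** The point holds in limited form and should be changed. The between-group method is left to the collected data, and the deciding rule is unstated. Linking the normality tests to the choice is a reading of two neighbouring sentences, but the section offers no other criterion.

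On perfectly normal data the switch rate is anywhere from about 10% to 59%, depending on the rule. The verdict then differs between tests in roughly 5-8% of trials at the planned effect, and in about 22% in the strongly skewed scenario. Type I error stays near 5%. These figures rest on assumed distributions and, for the three-outcome runs, uncorrelated outcomes.

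Separately, the sample size of 66 reproduces exactly as a comparison of mean GARS-2, while neither named between-group method directly estimates that difference or uses the baseline score. This is a mismatch between sizing and analysis, not an error in the sample size.

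**What to change.** Remove the normality-dependent switch from the between-group comparison and name one method in advance. For GARS-2 total, the outcome used for sizing, compare the arms at the 12-week post-test with a linear model adjusted for baseline GARS-2. Report the adjusted mean difference with its 95% CI, on a scale that can be set against the 1.175-point planning value. Keep a rank-based or bootstrap version as a sensitivity analysis, reported whatever the normality checks show.

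Apply the same model to BMI and MUAC. Their place among the primary outcomes is for the sponsor to decide and is not settled by this change.

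The cost is a few sentences in the Data analysis section, with no extra participants, visits or measurements. The price is slightly less power than ranks if scores prove strongly skewed. The article reports that recruitment has begun, so the choice should be recorded and dated before outcome data are examined.

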There have been several systematic reviews and meta-analyses [14–16] conducted on the nutrition of ASD children. There are different opinions on dietary interventions for ASD in Adolescents [12, 17, 18]. It is assumed that gluten-free and casein-free diets can minimize the symptoms of ASD, but there are controversial theories about the effectiveness of the gluten-free and casein-free (GFCF) diet [17]. According to certain studies, the GFCF diet can assist with symptoms such as stereotyped attitude, cognitive and social function, attention, interaction, and mood [18]. Many explanations have been proposed to explain how the GFCF diet improves the features of autism. Of all of these, the opioid excess hypothesis is the most widely accepted. Gluten and casein both affect the central nervous system via the leaky gut, but opioids escape via inflamed and thinning stomach in children with ASD [12].

Therapeutic interventions are multidisciplinary approaches [19] that, composed of balance [20], gait training [21], Therapeutic horse riding [22], motor training [23], strength training [24], aerobic exercise [25], and executive functional tasks [26]. It is hypothesized that structured dietary intervention adjunct with regular treatment approaches may have a greater benefit in children with ASD but no such research in Bangladesh has been held yet. It is important to determine the combined outcome of a structured diet (SD) and regular therapy (RT) for improving nutritional status and behavioral indices in the child and adolescents with malnutrition having Autism in Bangladesh.

The study objectives are to (1) determine the socio-demographics and anthropometric measures related to malnutrition for ASD in Bangladesh, (2) to elicit the within-group difference between structured diet (SD) with regular therapy (RT) or usual diet (UD) with regular therapy (RT) therapy on nutritional status and behavioral indices in post-test (3months) and follow-up (6months) compared to baseline, and (3) to find out the effectiveness among groups (SD with RT versus UD with RT) and observations (pretest to post-treatment, pretest to follow up, and post-test to follow up) comparison in the improvement of nutritional status and behavioral indices.

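### The arms are compared by an unadjusted multivariate test that is not the GARS-2 comparison behind the sample size, and post-test-to-follow-up change has no between-group test

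*Protocol article*

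**What the plan says.** The third objective, at the end of the Introduction, is "to find out the effectiveness among groups (SD with RT versus UD with RT) and observations". The observations listed there are three: pretest to post-treatment, pretest to follow-up, and post-test to follow-up. The second objective separately asks for within-group differences.

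The Data analysis section sets out two kinds of test:

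- Between groups: "The baseline compatibility, between-group post-test, and follow-up variations among the groups will be assessed using MANOVA or the Multivariate Kruskal-Wallis (MKW) test", the choice depending on the nature of the data.
- Over time, by repeated-measures or Friedman ANOVA: "Three measures will be analyzed within-group using an ANOVA, and additional post-hoc analyses will be performed using paired sample t-tests or Wilcoxon tests".

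The section does not say which variables enter the MANOVA. The primary outcome section lists GARS-2 together with several anthropometric measures.

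The Sample size section works from one outcome, "estimating the key outcome as the score of the Gilliam Autism Rating Scale (GARS 2) second edition". Its anticipated values "were estimated as 4.7±1.7 (0–10 Hiva scale converted from 0–126 GARS 2 score) with a baseline of 25% minimal clinical improvement", and it ends: "80% power, and with the alpha value 0.05, the total sample stands as of 66". Seventy are to be enrolled, 35 per arm.

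**The concern.** Three parts of the protocol do not line up: the objective, the test and the sample size.

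- **Objective against test.** Objective 3 combines groups and observations. The plan compares groups visit by visit and compares observations arm by arm. Nothing named joins the two, such as an arm-by-visit term or a comparison of change between arms.
- **Sample size against test.** The trial is sized for a difference in GARS-2. A MANOVA tests whether the arms differ on any of the variables entered, so its power depends on effects and correlations that the protocol does not give.
- **Baseline.** A pre-test is taken from every participant, but the between-group analysis makes no use of it beyond a check of comparability.

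At stake are the power and clarity of the randomised comparison, and the risk that within-arm results are read in its place. Both arms receive regular therapy and are observed for about nine months, so change within an arm is not the effect of the diet.

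**Working it through.** **Inputs.** From the Sample size section: mean 4.7 and SD 1.7 on the 0–10 scale, 25% improvement, power 80%, alpha 0.05, 1:1 allocation, 35 enrolled per arm. Alpha is taken as two-sided, because one-sided would give 52 in total. The baseline-to-post correlation r, the number of variables in the MANOVA, and their effects and correlations are not in the document; they are assumed below over a range.

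**1. The plan's own figure.** Difference = 0.25 × 4.7 = 1.175. Standardised difference d = 1.175 / 1.7 = 0.691.

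n per arm = 2 × [SD × (z₀.₉₇₅ + z₀.₈₀) / difference]² = 2 × [1.7 × (1.960 + 0.842) / 1.175]² = 32.86, so 33 per arm and 66 in total. This matches exactly. The calculation is for an unadjusted two-group comparison of one mean. With 35 per arm, power is 82.4% by the normal approximation and 81.3% by the noncentral t.

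**2. Using baseline.** Adjustment multiplies the residual SD by √(1 − r²), so the standardised effect becomes d / √(1 − r²). Noncentral t, 35 per arm, 67 degrees of freedom:

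| Assumed r | d / √(1 − r²) | Power |
|---|---|---|
| 0 (no gain) | 0.691 | 81.3% |
| 0.3 | 0.725 | 84.8% |
| 0.5 | 0.798 | 90.8% |
| 0.7 | 0.968 | 97.9% |

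Unadjusted change scores are not a safe substitute. Their SD is 1.7 × √(2(1 − r)), and power by the normal approximation is 68.6% at r = 0.3, 82.4% at r = 0.5 and 96.2% at r = 0.7, against 82.4% for the unadjusted post-test comparison.

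**3. Pooling outcomes.** For a two-group MANOVA (Hotelling T²) with p outcomes, the noncentrality is (n/2) × δ′Σ⁻¹δ on p and 2n − p − 1 degrees of freedom. With n = 35 and p = 3 (3 and 66 degrees of freedom):

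| Assumed pattern | δ′Σ⁻¹δ | Noncentrality | Power |
|---|---|---|---|
| Only GARS-2 moves, outcomes uncorrelated | 0.691² = 0.478 | 17.5 × 0.478 = 8.4 | 64.7% |
| Others move half as much, correlation 0.3 | 0.478 × 1.071 = 0.512 | 9.0 | 68.0% |
| All move equally, correlation 0.3 | 0.478 × 3 / 1.6 = 0.896 | 15.7 | 91.3% |

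The univariate reference is 81.3%. These are scenarios, not bounds.

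**4. Which contrasts are tested between arms.** Under randomisation the arms have the same expected baseline. The expected difference at post-test then equals the expected difference in pretest-to-post change, and likewise for follow-up. Two of the three contrasts are thus addressed. The third is the follow-up difference minus the post-test difference. Separate tests at the two visits do not test it.

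**5. Whether within-arm tests can fill the gap.** If true change is the same in both arms and each within-arm test has power p, one arm is significant and the other not with probability 2p(1 − p): 42% at p = 0.3, 50% at p = 0.5 (the maximum) and 32% at p = 0.8. Such a pattern is no evidence of a difference between arms.

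**The case against.** The strongest reply is that the plan does compare the arms. A reader might infer that no planned test answers objective 3; the protocol does not support that, because the post-test and follow-up comparisons cover change from baseline for two of the three contrasts. The phrase about follow-up variations is also loose enough to be read as change, although no test of change between arms is named.

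A reader might also infer that the within-arm tests are meant as proof of efficacy. The protocol does not say so: objective 2 asks for them in their own right. The risk lies in how they may be read.

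Nor can it be said that pooling outcomes costs power. The variables are not named, and in a diet trial the anthropometric measures may well move, in which case the multivariate test can gain. The benefit of baseline adjustment likewise depends on an unstated correlation. An unadjusted GARS-2 test would keep its designed power, so leaving baseline out is an inefficiency and not an error.

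Finally, model terms are often left to an analysis plan, which is not shown, and GARS-2 might be reported separately after the MANOVA. That would explain silence. Here, however, the article names its tests, and the test named is not the one that the sample size supports.

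**Conclusion.** The point holds in a limited form. Three things are firm and rest on the text alone:

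- The 80% power was calculated for a univariate GARS-2 comparison and does not carry over to the multivariate test.
- That test alone yields no GARS-2 effect estimate.
- The post-test-to-follow-up contrast in objective 3 has no between-group test, and the within-arm tests cannot supply one.

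The size of the power effects rests on assumptions. At 35 per arm and the planned effect, baseline adjustment adds nothing at r = 0 and about 4, 10 and 17 percentage points at r = 0.3, 0.5 and 0.7. Pooling three outcomes gives anything from about 65% to 91% in the scenarios shown, so its direction is unknown.

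**What to change.** Make the primary analysis a baseline-adjusted between-group comparison of GARS-2 total: ANCOVA, or a mixed model with arm, visit, arm-by-visit and baseline GARS-2. Report the adjusted difference with 95% CI at 12 weeks and at follow-up, and the difference between those two for the post-test-to-follow-up contrast. Analyse the anthropometric outcomes in separate models of the same form. Keep within-arm change for objective 2 as description, and state that it is not evidence of efficacy.

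The cost is a change of wording and a little more analysis work, with no extra data. Recruitment has started, so the change should be documented before outcome data are examined. It will not remove the confounding of arm with centre and assessor that follows from the Study setting and Study procedure sections, where each arm has its own centre and each centre its own assessor. That is a separate issue, which no choice of model can repair.
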